### Data collection and management

To ensure the competence in managing the project, data collectors, researchers and coordinators involved in the study will receive a thorough training in advance. The coordinators at each centre will utilise an electronic data acquisition system for inputting the CRF information. The specific system being used has obtained copyright for its computer software on 6 April 2022 (software no. 9387742). After data entry, a designated individual will regularly perform accuracy checks to ensure the integrity of the entered data. If any data revisions are necessary, the modified data will undergo review by the data manager. Data access will be strictly restricted to authorised personnel only. The principal investigators at each centre will have the ability to log into the system and view the data, but access to full information will only be granted with permission from the coordinating investigators of the research. It is emphasised that all research-related documents will be treated as highly confidential and stored securely at the study site.

### Data monitoring

An independent Data and Safety Monitoring Board () will assume responsibility for data monitoring and blinded analysis in this trial. DSMB committee members will regularly review the research data to ensure its integrity. Furthermore, the trial will undergo examination by the medical EC of each participating centre, which will assess its adherence to ethical principles and guidelines.

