The safety endpoint of the study includes the assessment of any AEs, including serious adverse events (SAEs) and adverse drug reactions (ADRs). These ADRs may manifest as various symptoms, such as head swelling, dyspnoea, convulsion, diplopia, purpura, bleeding tendency, allergies, and others.

During clinical research, it is essential for researchers to closely observe any AEs experienced by subjects. When AEs are identified, researchers should promptly take appropriate measures based on the subjects’ conditions. Regardless of whether the AEs are associated with LA injection or not, it is necessary for researchers to diligently record them in detail within the case report form (CRF). The recorded information regarding AEs should encompass a description of the events, their occurrence time, severity, duration, measures taken, final results and outcomes. These records serve the purpose of analysing the potential correlation between AEs and LA injection, and they need to be signed and dated. In the event of encountering any SAEs, it is mandatory to report them to the principal investigator of the trial, the ethics committee (EC) and the state supervision agency within 24 hours of their occurrence. When an AE is identified, the researcher can administer necessary treatment measures considering the subject’s condition, such as dose adjustment or temporary suspension of research drug usage. The decision regarding whether to terminate the study will depend on the circumstances. In case of an SAE occurrence, immediate action must be taken by the researcher to safeguard the safety of the subjects.

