#### Security set (SS)

The SS comprises all actual cases that have received at least one administration of the assigned fluid as per randomisation. This set includes participants for whom safety endpoints are recorded, allowing for the assessment of AEs. The incidence of AEs is calculated based on the number of patients included in the safety set. By analysing the safety data from this set, researchers can evaluate the occurrence and severity of AEs related to the administered fluid, providing important insights into the safety profile of the treatment.

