### Statistical analysis

All analyses, including the primary analyses, will be conducted in accordance with the ITT principle. The data will be analysed using R software V.3.3.3 (R Foundation for Statistical Computing, Vienna, Austria) and RStudio V.1.0.136 (RStudio, Boston, MA, USA). Descriptive statistics will be used to describe the data’s distribution, with continuous data presented as mean (SD) or median and IQR, depending on the data characteristics. Categorical data will be reported as number and percentage. Group comparisons will be conducted using group t-tests or analysis of variance for continuous data assuming normality, and non-parametric tests will be used if normality assumptions are not met. Categorical results will be compared using χ^2^ test or Fisher’s exact test. The statistical significance level for all tests will be set at a p value of less than 0.05.

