### Interim analysis

No interim analysis is scheduled for this trial.

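### The article provides no by-arm comparison of deaths or SAEs during the trial; separately, its safety set drops patients who received only the other arm's fluid

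*Protocol article*

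**What the plan says.** **Monitoring.** Under Data monitoring, an independent Data and Safety Monitoring Board "will assume responsibility for data monitoring and blinded analysis in this trial". The only purpose given for its reviews is data integrity: "DSMB committee members will regularly review the research data to ensure its integrity". The Interim analysis section is one sentence, "No interim analysis is scheduled for this trial", and does not limit itself to efficacy. Evaluation and outcomes requires every AE to be recorded, related or not, and SAEs to go to the principal investigator, "the ethics committee (EC) and the state supervision agency within 24 hours of their occurrence".

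**Safety set.** The Security set section says: "The SS comprises all actual cases that have received at least one administration of the assigned fluid as per randomisation". It then makes this set the denominator for safety: "The incidence of AEs is calculated based on the number of patients included in the safety set". It gives no rule for the arm under which a patient is counted if the fluid received differs from the fluid assigned. Statistical analysis adds: "All analyses, including the primary analyses, will be conducted in accordance with the ITT principle".

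**The concern.** These are two separate faults.

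1. The board's analysis is blinded, its review is framed as integrity checking, and interim analysis is excluded without qualification. Together these leave no stated route by which an excess of deaths or SAEs on LA would be compared between arms while patients are still being enrolled. The primary endpoint is death, the assumed control mortality is high, and the Introduction says human studies of LA in sepsis are lacking. At stake is protection of patients during enrolment.

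2. A safety set normally follows exposure. This one follows assignment at the point of entry, so a patient exposed only to the wrong fluid contributes neither events nor denominator. At stake is whether the final AE rates describe what patients actually received.

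**Working it through.** **Monitoring: the passages side by side.** Data monitoring says what the board does (blinded analysis, integrity review). Interim analysis says what will not happen (any interim analysis). Evaluation and outcomes supplies case-by-case SAE reporting. None of the three describes a table of deaths or SAEs by arm during the trial. With 38.2% of controls expected to die, a single death is not a signal; only a comparison of rates can show an excess.

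**Monitoring: illustration of size.** The plan has no figure of its own to reproduce here.

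- From Sample size: control 28-day mortality 38.2%; 176 per arm.
- Assumed: LA mortality of 45%, 50% or 55%; by-arm looks after one third and two thirds of patients (176/3 = 58.7, taken as 59; 2 × 176/3 = 117.3, taken as 118); complete 28-day outcomes at each look; a flag if z > 2.0 in the direction of harm.
- Formula: z = (p_LA − p_placebo) / √[2·p̄(1 − p̄)/n], where p̄ is the pooled death rate and n the number per arm. Flag probabilities come from exact binomial probabilities summed over both looks.

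| LA mortality | Relative risk | Flag at look 1 | First flag at look 2 | Either look | Excess LA deaths at 176 per arm |
|---|---|---|---|---|---|
| 38.2% (no effect) | 1.00 | 2.3% | 1.5% | 3.9% | 0 |
| 45% | 1.18 | 11.2% | 9.9% | 21.1% | 176 × 0.068 = 12.0 |
| 50% | 1.31 | 25.5% | 21.5% | 47.0% | 176 × 0.118 = 20.8 |
| 55% | 1.44 | 45.8% | 29.1% | 74.9% | 176 × 0.168 = 29.6 |

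The last column does not count deaths that the looks would avert. At 50%, if every flag halted enrolment at once, the average averted would be about 0.255 × (176 − 59) × 0.118 + 0.215 × (176 − 118) × 0.118 = 3.5 + 1.5 = 5.0. The 28-day wait for outcomes would lower this.

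**Would a pooled, blinded death rate do instead?** Take 176 patients in total (88 per arm) and test the pooled rate against exactly 38.2% at one-sided 0.025; the flag is 81 or more deaths.

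| Relative risk (assumed) | Pooled check, 176 patients | One by-arm look, 88 per arm |
|---|---|---|
| 1.2 | 16% | 17% |
| 1.3 | 31% | 33% |
| 1.4 | 51% | 53% |
| 1.5 | 70% | 72% |

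The power is similar, but only if the true control rate is known to be 38.2%. At a relative risk of 1.3 the pooled rate is 0.382 × (1 + 1.3)/2 = 43.9%. A trial with no treatment effect and a true mortality of 43.9% in both arms would look the same. The pooled rate cannot attribute an excess to an arm.

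**Safety set: reading the definition through.**

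- Given the assigned fluid only: in the set, no difficulty.
- Given only the other arm's fluid: never received the assigned fluid, so out of the set and out of AE incidence.
- Given both fluids: in the set, but the section does not say under which arm.
- Given neither: out of the set, as usual.

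The documents give no expected number for the second or third case, so their effect on AE rates cannot be computed.

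**The case against.** **A by-arm comparison may exist.** Blinded analysis can mean tables by coded arm, a statement that there is no interim analysis often refers only to efficacy looks, and a board charter is usually a separate document. This stands against the stronger reading that nobody compares deaths by arm, or that harm cannot be seen: the article does not say so. What remains is that its two sentences, as worded, provide no such comparison, and a charter that did would have to be reconciled with both.

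**Other safeguards exist.** SAEs are reported within 24 hours, ethics committees examine the trial at each centre, and in a single-blind trial investigators may know the arm. These are genuine case-level safeguards. They do not produce a comparison of rates across eight centres.

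**The illustration rests on assumed harm.** This is correct. No document gives an LA mortality above control, and at the assumed 50% more than half of trials would pass both looks unflagged. A reader might infer that about 21 deaths would be prevented; the working shows why that does not follow.

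**The safety-set fault is minor.** Largely accepted. A reader might infer that it could hide deaths, but mortality is analysed by ITT in everyone randomised. A reader might also infer that a patient given both fluids counts as placebo; the Security set section does not say that, and only the general ITT sentence points that way. The Discussion calls LA a commonly used adjuvant in sepsis, but this mostly suggests LA given on top of assigned saline, and such a patient stays in the set. The set drops only those given solely the wrong fluid.

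**Conclusion.** Both points hold in limited form and should be corrected.

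1. As written, the article provides no aggregate by-arm review of deaths or SAEs during a mortality trial of a treatment that it says lacks human sepsis data. This is a conclusion about the text; it does not establish that no charter provides such a review. By-arm looks would have modest to useful sensitivity (about 21% to 75% across the assumed harms, with about 4% false flags), conditional on the 38.2% control rate, the assumed LA rates and the assumed timing and threshold.

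2. The safety set, read literally, removes patients given only the other arm's fluid from AE incidence and states no grouping by actual receipt. The effect is confined to AE rates. It probably concerns few patients, but the number is not given and could not be estimated.

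**What to change.** **Monitoring.** State in Data monitoring that, at the reviews already planned, the board receives deaths and SAEs by arm, coded or unblinded, in closed session only, for harm monitoring and with no stopping for efficacy. Reword Interim analysis so that it excludes interim efficacy analysis only. If a charter already says this, bring the two sections into line with it. No patients are added, and because there is no efficacy stopping, the primary type I error is not inflated. The small cost is a firewall between the board's tables and the trial team.

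**Safety set.** Define it as all patients who received any amount of either study infusion, analysed by the infusion actually received, with anyone who received any LA counted under LA. Exempt this set explicitly from the sentence that places all analyses under ITT. This is a change of wording only.

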### Analyses sets

The analysis of the trial will be conducted following the ‘intention-to-treat’ (ITT) principle. This means that all patients who have undergone randomisation, regardless of whether they completed the trial or received the designated treatment, will be included in the analysis according to their original assigned groups. The randomisation information will be retained to the maximum extent possible, ensuring that the integrity of the randomisation process is maintained during the analysis.

#### Intention-to-treat set (ITTS)

The principle of ITT analysis is adopted to retain the randomised information effectively and attribute differences in trial results to treatment variations. This ensures that the assessment of treatment effects, specifically in the case of LA treatment, is conducted in the most accurate manner possible. The ITT set (ITTS) consists of all patients who were randomised, regardless of whether they received their designated treatment or completed the full trial. All patients in the ITTS remain in their original assigned groups for analysis. By adhering to the ITT principles, the analysis maintains the integrity of the randomisation process and provides a comprehensive evaluation of the treatment’s effectiveness, accounting for the real-world scenario.

#### Per protocol set (PPS)

The PPS includes all participants who meet the eligibility criteria and receive treatment as per their assigned randomisation. These participants demonstrate good compliance with the trial protocol, including being prepared to receive treatment, undergoing measurements for primary efficacy endpoints and ensuring that the necessary information is filled in the CRF. The PPS is specifically utilised to analyse the primary efficacy endpoints of the study. By focusing on participants who adhere closely to the trial protocol, the PPS analysis provides insights into how the treatment performs under optimal conditions and can help evaluate the treatment’s efficacy in a controlled setting.

#### Security set (SS)

The SS comprises all actual cases that have received at least one administration of the assigned fluid as per randomisation. This set includes participants for whom safety endpoints are recorded, allowing for the assessment of AEs. The incidence of AEs is calculated based on the number of patients included in the safety set. By analysing the safety data from this set, researchers can evaluate the occurrence and severity of AEs related to the administered fluid, providing important insights into the safety profile of the treatment.

### Statistical analysis

All analyses, including the primary analyses, will be conducted in accordance with the ITT principle. The data will be analysed using R software V.3.3.3 (R Foundation for Statistical Computing, Vienna, Austria) and RStudio V.1.0.136 (RStudio, Boston, MA, USA). Descriptive statistics will be used to describe the data’s distribution, with continuous data presented as mean (SD) or median and IQR, depending on the data characteristics. Categorical data will be reported as number and percentage. Group comparisons will be conducted using group t-tests or analysis of variance for continuous data assuming normality, and non-parametric tests will be used if normality assumptions are not met. Categorical results will be compared using χ^2^ test or Fisher’s exact test. The statistical significance level for all tests will be set at a p value of less than 0.05.

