### Evaluation and outcomes

Participants in the study will undergo clinical evaluation and laboratory testing, as outlined in online supplemental table 1. The collected data will include demographic information such as age and gender, disease diagnosis and progression, interventions and prognosis, as well as adverse events (AEs). The disease diagnosis data will encompass primary and concomitant diseases, blood culture results, white blood cell count and liver and kidney biochemistry. Disease progression data will involve baseline severity scores and serum biomarkers, including Sequential Organ Failure Assessment (SOFA) score, Acute Physiology and Chronic Health Evaluation II (APACHE II) score, procalcitonin (PCT), high-sensitivity C-reactive protein (hs-CRP), interleukin 2 (IL-2), IL-4, IL-6, IL-10, tumour necrosis factor-α (TNF-α) and interferon-γ (IFN-γ). Follow-up values on specific days (day 1 (D1), D3, D5, D7) after randomisation will also be recorded, along with the changes from baseline.

10.1136/bmjopen-2023-072897.supp2Supplementary data

Data related to disease intervention will include the requirement and duration of life support measures like mechanical ventilation, vasoactive drugs and continuous renal replacement therapy. Disease prognosis data will encompass 28-day all-cause mortality, ICU mortality, in-hospital mortality, incidence of new-onset acute kidney injury (AKI) after ICU admission, ICU stay and length of hospital stay. Throughout the study, data on organ dysfunction, occurrence of AKI and safety events will be continuously monitored.

The primary efficacy endpoint of the study is 28-day all-cause mortality. The secondary efficacy endpoints are as follows:

ICU mortalityHospital mortalityDuration of ICU and hospital stayIncidence of new AKI in ICUSOFA/APACHE II scores on specific days (D1, D3, D5 and D7) and their changes from baseline (ΔSOFA/ΔApache II)Demand and duration of life support measures (vasopressors, invasive mechanical ventilation and continuous renal replacement therapy).Lactate concentration of arterial blood on specific days (D1, D3, D5 and D7) and their changes from baseline (ΔLAC).Levels of PCT, hs-CRP, IL-2, IL-4, IL-6, IL-10, TNF-α and IFN-γ on specific days (D1, D3, D5, and D7) and their changes from baseline.The detection of levels of IL-2, IL-4, IL-6, IL-10, TNF-α, and IFN-γ is not mandatory if unavailable.

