### Sample size

In this study, the primary efficacy endpoint was the 28-day all-cause mortality rate. A large-scale epidemiological survey conducted in the ICU revealed that the control group had a 38.2% 28-day all-cause mortality rate. In an RCT comparing the LA injection treatment group, the relative risk reduction was approximately 0.33.^38^ The anticipated 28-day all-cause mortality rate for the treatment group was expected to be 22.9% with a one-sided test, using α=0.025 and β=0.2 (power=80%). The threshold value, Δ, was set at 0.

Participants are randomised at a ratio of 1:1, resulting in a calculated sample size of 160 for each group using a superiority test (where a lower rate is considered superior). Taking into account the anticipated dropout rate of around 10%, the sample size was increased to 176 cases in each group.

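### SOFA, APACHE II, lactate and eight biomarkers are to be compared without baseline adjustment, as both level and change, which costs precision and lets the two scales disagree

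*Protocol article*

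**What the plan says.** The protocol article gives one rule for all continuous outcomes, under Statistical analysis: "Group comparisons will be conducted using group t-tests or analysis of variance for continuous data assuming normality", while "non-parametric tests will be used if normality assumptions are not met". The threshold is common to every test: "The statistical significance level for all tests will be set at a p value of less than 0.05". That section names no baseline covariate, repeated-measures term or site term, although the Allocation section stratifies randomisation by site.

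The Evaluation and outcomes section sets the secondary endpoints to which this rule applies. SOFA and APACHE II are listed on four follow-up days, both as scores and as changes from baseline. Lactate appears as "Lactate concentration of arterial blood on specific days (D1, D3, D5 and D7) and their changes from baseline". The biomarkers appear as "Levels of PCT, hs-CRP, IL-2, IL-4, IL-6, IL-10, TNF-α and IFN-γ on specific days (D1, D3, D5, and D7) and their changes from baseline". Measurement of the six cytokines "is not mandatory if unavailable".

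The Sample size section rests on 28-day mortality alone: "resulting in a calculated sample size of 160 for each group using a superiority test", after which "the sample size was increased to 176 cases in each group". It makes no power statement for any continuous endpoint.

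**The concern.** Change from baseline is itself an endpoint, so a baseline value is needed for every one of these measures. The stated tests use that value inefficiently. A comparison of levels ignores it. A comparison of changes subtracts all of it, which over-corrects whenever the correlation between baseline and follow-up is below 1 (with equal SDs). Both therefore carry more noise than an analysis that lets the data set the weight on baseline.

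Listing both scales adds a second problem. If the arms differ at baseline by chance, the level comparison is pulled towards the arm difference at baseline and the change comparison is pulled the other way. The same marker on the same day can then give two different messages.

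These endpoints carry the trial's stated aims on inflammation and organ dysfunction. At stake is how clearly the trial can answer those secondary questions. The mortality result is not at stake.

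**Working it through.** **Number of comparisons (plain reading of the two sections together)**

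- SOFA and APACHE II: 2 × 4 days × 2 scales = 16
- Lactate: 1 × 4 × 2 = 8
- Biomarkers: 8 × 4 × 2 = 64, of which the six optional cytokines make 6 × 4 × 2 = 48
- Total: 16 + 8 + 64 = 88

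**Precision.** The documents give no SD, correlation or power for these endpoints, so there is no stated figure to reproduce. Assume equal baseline and follow-up SDs and a correlation r of 0.3, 0.5 or 0.7. The large-sample variance of the arm difference, in units of 2·SD²/n, is:

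- level: 1
- change: 2(1 − r)
- baseline-adjusted (ANCOVA): 1 − r²

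| r | Level | Change | ANCOVA | ANCOVA ÷ level | ANCOVA ÷ change |
|---|---|---|---|---|---|
| 0.3 | 1 | 1.40 | 0.91 | 0.91 | 0.65 |
| 0.5 | 1 | 1.00 | 0.75 | 0.75 | 0.75 |
| 0.7 | 1 | 0.60 | 0.51 | 0.51 | 0.85 |

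The direction does not depend on r: level minus ANCOVA is r², and change minus ANCOVA is 2(1 − r) − (1 − r²) = (1 − r)². Neither can be negative.

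In terms of power, take an effect for which the level t-test has 80% power (two-sided 0.05, 160 per group). Its standardised size is 1.96 + 0.84 = 2.80. Power on another scale is Φ(2.80/√V − 1.96), where V is the variance in the table.

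| r | Level | Change | ANCOVA |
|---|---|---|---|
| 0.3 | 80% | 65.8% | 83.6% |
| 0.5 | 80% | 80.0% | 89.9% |
| 0.7 | 80% | 95.1% | 97.5% |

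**Chance imbalance.** Suppose the arms differ at baseline by 0.2 SD. With 160 per group the standard error of that difference is √(2/160) = 0.112 SD, so this is 0.2/0.112 ≈ 1.8 standard errors. With no treatment effect, the expected level difference is r × 0.2 and the expected change difference is (r − 1) × 0.2. The conditional type I error follows from that shift, a conditional variance of 1 − r², and the critical value that the unadjusted test uses.

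| r | Level shift (SD) | Change shift (SD) | Type I error, level | Type I error, change |
|---|---|---|---|---|
| 0.3 | +0.06 | −0.14 | 7% | 13% |
| 0.5 | +0.10 | −0.10 | 11% | 11% |
| 0.7 | +0.14 | −0.06 | 16% | 9% |

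The adjusted comparison stays at 5%. For an imbalance of 0.1 SD, the unadjusted error rates are 3% to 5%, at or below nominal. These small and large imbalances offset each other, which is why the tests hold their level over all randomisations.

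**Why adjustment removes the conflict.** If change is modelled as Y − X = a + b·arm + c·X, then Y = a + b·arm + (c + 1)·X. The arm effect b is the same for level and change, provided both are on the same scale.

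**The case against.** The strongest objection is that the tests are valid and the rest is preference or detail for an analysis plan that is not shown. Much of this stands.

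- A reader might infer that the protocol orders a separate test at each visit on each scale. It does not say so. The count of 88 comes from reading one general sentence against the endpoint list. Analysis of variance is also named, and a repeated-measures form is not excluded. With two arms, though, a one-way analysis of variance is the t-test, and neither form as stated includes baseline.
- A reader might infer that the comparisons are biased. Over randomisation they are not, and they keep their 5% level. The distortion exists only given a chance imbalance.
- A reader might turn the variance ratio of 0.75 into a trial with 25% fewer patients. The documents do not support that, because mortality alone sets the sample size.
- The ratios describe comparisons of means. Lactate, PCT, hs-CRP and the cytokines, nine of the eleven measures, are plausibly skewed and may go to rank tests, where these figures do not apply directly. They fit SOFA and APACHE II best.
- Transformations, the choice of contrast and precedence between scales may properly sit in an analysis plan, so their absence is not the finding.

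What survives is the method that the protocol does state. It is unadjusted for measures whose baseline is collected, and it applies to two scales that can contradict each other.

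**Conclusion.** The concern holds as a matter of efficiency and clarity for secondary endpoints and should be addressed. Under equal SDs and an assumed correlation of 0.3 to 0.7, baseline adjustment lowers the variance of a mean comparison by 9% to 49% against the level test and by 35% to 15% against the change test. The size depends on the correlation, which the documents do not give. The direction, in large samples, does not.

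The risk of conflicting answers is conditional: it matters when a noticeable baseline difference happens to occur. The stated tests are not invalid, and nothing here touches the 28-day mortality comparison or the planned 176 per group.

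**What to change.** In the Statistical analysis section, replace separate level and change tests for the 11 measures with one baseline-adjusted analysis per marker. This can be ANCOVA at a named day, or a repeated-measures model with baseline, arm, day, arm-by-day and site. Name one contrast per marker in advance.

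Four details need stating with it:

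- **Skewed markers.** Fix a log scale in advance, with baseline also logged, and report an adjusted ratio. This ratio replaces the absolute change as the tested effect, because the equality of level and change holds only on a common scale. Keep absolute change, including ΔLAC, as description only.
- **Deaths before D7.** With 38.2% control-arm mortality at 28 days assumed in the Sample size section, some early deaths are likely. A standard repeated-measures model implicitly extrapolates values beyond death, so say how these patients enter the analysis.
- **Early discharge.** Say likewise how patients discharged before D7 are treated.
- **Cytokines.** Limit these analyses to sites that measure them.

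The cost is wording, settled before any unblinded analysis. No new data or patients are needed. The small downside is that log-scale markers are reported as ratios rather than absolute changes.
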